## Discussion

This innovative study will be the first to document the effectiveness of an intervention combining motivational interviews and IT support to improve the lifestyle habits of women with overweight or obesity without a history of infertility in the preconception period (34, 35). Furthermore, it will be the first study to include male or female partners in the evaluation of a preconception intervention (36). In addition to documenting the impact of the intervention on the lifestyle habits and anthropometric indices of partners, this analysis will provide insight on the impact of sex and gender in the response to interventions, and will allow us to explore whether the participation of both members of the couple is of added benefit for the achievement of lifestyle goals by each participant.

The body of evidence produced in this trial will be useful to guide future research endeavors on obesity prevention in preconception and pregnancy. This study will document the impact of the intervention on nutritional behaviors in preconception and will provide evidence regarding the plausibility of an effect of the intervention on health outcomes in the preconception period and pregnancy. If the intervention produces positive dietary changes which are sustained through the preconception period and pregnancy, a larger trial will be warranted to assess the effects of the intervention on clinical outcomes of pregnancy.

The use of urinary metabolomic profiling will also allow us to explore possible associations between epidemiological measures of diet and biological (metabolomic) indictors that may reflect dietary changes produced by the intervention. This profiling appears particularly promising as it is an objective means of evaluating dietary intake and is not subject to recall bias. If the metabolite derived diet quality score can be correlated with the C-HEI both in preconception and pregnancy, urinary dietary exposure biomarkers could be used as the sole measure of dietary intake and quality in future studies.

We will also document several measurements of the feasibility of targeting couples with no history of subfertility in the preconception period including recruitment rates, attrition rates, effective recruitment and retention strategies, and pregnancy rates within a 12-month preconception period. No similar study has been registered on the platforms clinicaltrials.gov or on the International Clinical Trials Registry Platform.

The methodology of this trial presents several strengths. Firstly, our intervention was designed to be in line with both the UK Medical Research Council statement on the development and evaluation of complex interventions, and the Consort statement for the reporting of non-pharmacologic interventions (84, 85). Indeed, our intervention is based on a recognized behavior change model, specific intervention targets have been outlined, and the behavior change techniques at play have been well-described. These elements will improve the likelihood of intervention success and allow replication of the intervention if it is proven to be effective. Secondly, we have chosen to document the effectiveness of the intervention on metabolic risk factors in the preconception period prior to conducting a large clinical trial with sufficient power to detect differences in clinical outcomes. This first step in evaluating a complex behavioral intervention is in line with the Orbit recommendations (40) and will avoid a waste of resources if the intervention appears to be ineffective. This will also avoid the limitations in outcome assessment found in the RADIEL trial (38), where the measure of the primary outcome in pregnancy, when randomization took place in preconception, severely compromised the validity of the results. Thirdly, the choice of an explanatory randomized controlled trial design will provide good internal validity to document the effects of the intervention. Lastly, our methodology includes a detailed and systematic approach to recruitment, retention, and adverse event monitoring which will all contribute to the validity and success of the study.

This study presents several limitations. First, our choice of diet quality in preconception as our primary endpoint, which is an intermediate variable for clinical outcomes, will limit the direct relevance of this study for clinical practice. Diet quality in preconception is also controversial, as two large cohort studies have reported that adhering to a combination of healthy habits including high diet quality, physical activity, being a non-smoker, low stress, and a normal BMI is more protective against the occurrence of GDM than any one of these factors alone (86, 87). However, for the purposes of sample size calculation, a single primary outcome had to be chosen and diet quality appears as the most predictive of pregnancy outcomes and is more sensitive to change (41–44, 58). Second, given the nature of the intervention, the masking of participants and the project coordination team to the study group will not be possible. Diet quality will be measured through an online 24-h dietary recall and urine samples, and the other lifestyle habits scores will be collected with the use of self-reported questionnaires to limit social desirability. Lastly, the strict selection of study participants could induce a selection bias and will limit the external validity of this trial. To limit this potential bias, we will use various recruitment methods to contact participants from diverse socioeconomic and cultural backgrounds and the baseline characteristics of participants in each group will be reported with our results.

We report the rationale and methods of an innovative randomized controlled trial evaluating the effectiveness of a low-cost intervention to support adoption of healthy lifestyle habits for women with overweight or obesity in the preconception period. This study will provide useful information on the feasibility of preconception trials, and on the potential of preconception interventions to prevent complications of overweight and obesity. This study will also help establish whether urinary metabolomic profiling can be used as a reliable and objective measure of diet quality in preconception and pregnancy. If the *Healthy for my Baby* intervention significantly improves lifestyle scores in women with overweight or obesity during preconception, larger trials will be needed to directly evaluate the impact of this intervention on clinical outcomes. Ultimately, if proven effective, this intervention could be integrated in regular clinical practice to help improve the health of couples, pregnant women and their babies. Future large-scale implementation of this intervention in diverse clinical settings will be facilitated by its low cost, ease of use and accessibility.

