**Exploratory Objectives:**

To evaluate the correlation between women's C-HEI score and the metabolite derived diet quality score in preconception and pregnancy.To explore untargeted metabolomic phenotypes within the study population to find associations between metabolism and eating patterns during pregnancy.

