### Sample Size Calculation and Analysis Plan

#### Sample Size Calculation

Since no minimally clinically important effect size has been defined for the HEI score, our effect size has been estimated as a plausible effect of the intervention based on the preliminary results of the *Obesity Fertility* trial (71), which demonstrated a 12.5 ± 13.0 points increase in the average HEI score of women with obesity and infertility after a 6-month lifestyle intervention (unpublished data). An increase of 12 points in the average HEI score was also observed in breast cancer survivors with obesity who received a 6-month dietetic intervention (75). To detect a 10% difference in the average HEI score between groups with a 13-point standard deviation, an alpha value of 5% and 80% power, we will need to recruit 27 women per group (76). To account for a 20% attrition rate (77), a total of 68 women and their partners will be recruited.

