#### Statistical Analysis Plan

Study results will be analyzed at the end of the trial following intent-to-treat principles. Participants' baseline characteristics will be reported to assess group comparability at baseline in preconception and at the beginning of pregnancy. A statistical significance threshold of 5% will be used for all analyses. Statistical analyses will be performed using the Statistical Package for the Social Sciences (SPSS version 26) and R (Version 4.0.2) software. No interim analysis will be performed.

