#### Secondary Outcome Analysis

For the main secondary outcome for the pregnancy phase of the trial, we will use a Chi-squared test to compare the proportion of women who have an adequate gestational weight gain in each group.

For the targeted analysis of urine biomarkers, the concentration of around 40 metabolites will be compared between baseline, 2 months in preconception and 24–26 weeks of pregnancy using repeated measures ANOVA or Friedman test with a Bonferroni adjustment for multiple comparisons. The correlation between the metabolite derived diet quality score and the C-HEI score will be evaluated using Pearson's correlation.

Although our sample size is fairly small, an exploratory multivariate analysis of non-targeted metabolome profiles will be realized using both unsupervised ‘natural clustering’ analysis and Supervised Random Forest classification.

For the other secondary outcomes, continuous variables will be assessed using Student's *t*-tests or Mann-Whitney tests as appropriate. Dichotomic variables will be analyzed using Chi-squared tests or Fisher's exact test as appropriate.

For participants who achieve a pregnancy prior to the 2-month food recall and/or 3-month preconception visit, lifestyle and anthropometric outcomes at the first pregnancy visit will be used to complete the preconception analysis. Women will be able to signal the occurrence of a pregnancy through the mobile application as soon as a period is missed. The application software will immediately notify the research team which will allow completion of data collection prior to the occurrence of significant pregnancy symptoms such as hyperemesis.

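### A Pearson correlation with no minimum strength cannot support urine as the only diet measure, because change in the urine score is never compared with change in the C-HEI

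*Protocol article*

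**What the plan says.** The protocol article lists the comparison under Exploratory Objectives: "To evaluate the correlation between women's C-HEI score and the metabolite derived diet quality score in preconception and pregnancy". Secondary Outcome Analysis gives the method: "The correlation between the metabolite derived diet quality score and the C-HEI score will be evaluated using Pearson's correlation". It sets no minimum value of r and no confidence limit, and does not say whether visits are taken separately or pooled. The only threshold in the article is the general one under Statistical Analysis Plan: "A statistical significance threshold of 5% will be used for all analyses".

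The Discussion then states what would follow. The condition is "If the metabolite derived diet quality score can be correlated with the C-HEI both in preconception and pregnancy" and the consequence is that "urinary dietary exposure biomarkers could be used as the sole measure of dietary intake and quality in future studies". Its closing paragraph adds that the study will help "establish whether urinary metabolomic profiling can be used as a reliable and objective measure of diet quality in preconception and pregnancy".

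Urine is also examined over time. The preconception objectives include the effect of the intervention on urinary indicators at 2 months. Secondary Outcome Analysis compares about 40 metabolite concentrations across baseline, 2 months and 24–26 weeks. The Diet Quality section cites an outside crossover trial for the sensitivity of urinary profiling to change.

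**The concern.** A correlation between two scores measured at the same visit shows that women who rank higher on one tend to rank higher on the other. It does not show that one can stand in for the other. The recall-based C-HEI has a specific job in this trial: under Primary Outcome Analysis, the endpoint is the difference between groups in how the score evolves over time. A replacement measure must move when a woman's diet moves, and a correlation of levels does not test that.

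At stake is the choice of outcome measure for the larger trial that the article anticipates. A modest correlation could be cited as grounds for dropping dietary recall. The trial would also pass over a useful comparison in an unmasked study: whether a woman's self-reported gain is matched by her own urine marker.

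**Working it through.** **The plan's own figure.** The sample-size section states "with a 13-point standard deviation, an alpha value of 5% and 80% power, we will need to recruit 27 women per group", for a difference of 10 (given as 10% of a 100-point score). Two-sided: n = 2 × (1.96 + 0.842)² × 13² / 10² = 2 × 7.85 × 1.69 = 26.5, so 27 per group. Then 54 / 0.80 = 67.5, which gives the plan's 68: "To account for a 20% attrition rate (77), a total of 68 women and their partners will be recruited". Both figures reproduce, so 68 (all recruited) and 54 (after attrition) are the natural limits for preconception.

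**Smallest r that reaches p<0.05.** Assumptions: correlated means significant, the test is two-sided, and there is one pair of scores per woman. The article states none of these. Formula: r = t / √(t² + n − 2), with t the 97.5% point on n − 2 degrees of freedom. At n = 68: 1.997 / √(3.99 + 66) = 0.239. The 95% CI is by Fisher z. The article does not give the number of pregnancies, so 20 to 45 is an assumed range.

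| Period | n | smallest r | r² | 95% CI at that r |
|---|---|---|---|---|
| Preconception | 68 | 0.24 | 6% | 0.00 to 0.45 |
| Preconception | 54 | 0.27 | 7% | 0.00 to 0.50 |
| Pregnancy (assumed) | 45 | 0.29 | 9% | 0.00 to 0.54 |
| Pregnancy (assumed) | 34 | 0.34 | 12% | 0.00 to 0.61 |
| Pregnancy (assumed) | 20 | 0.44 | 20% | 0.00 to 0.74 |

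If the two preconception visits of 68 women were pooled as 136 independent pairs, the smallest r would fall to 0.17 (3%).

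**Levels versus change.** Illustration with assumed variances: each score is a stable level (SD 1) plus independent visit-to-visit variation (SD 0.7), and the stable levels correlate at 0.6. The correlation at any one visit is 0.6 / (1 + 0.49) = 0.40. In the changes the stable levels cancel and only independent variation is left, so the correlation is 0. A simulation of 200,000 women gave 0.40 at each visit and 0.00 for the changes. An r that is significant at every sample size above except n = 20 is therefore compatible with no tracking of change.

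**Mixing of arms after baseline.** If both scores shift by d SD in one of two equal arms, a within-arm correlation r becomes (r + d²/4) / (1 + d²/4). With d = 10/13 = 0.77 for both scores (assumed), d²/4 = 0.148. Then r = 0 becomes 0.148 / 1.148 = 0.13, and r = 0.30 becomes 0.448 / 1.148 = 0.39.

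**The case against.** The strongest reply is that no decision rule exists to be faulted. The correlation is labelled exploratory, the Discussion sentence says only what could be done in future studies, and nowhere does the article equate correlated with p<0.05. This stands in part: the thresholds above rest on a reading, and the trial's own conclusions do not depend on it. But the article itself states both the method and the inference drawn from it, and that inference fails under any reading that relies on levels alone.

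Three stronger readings are tempting, and the documents do not support them.

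- *An r of about 0.25 would be enough to drop recall.* The condition requires both periods. An r of 0.25 gives p = 0.04 at 68 women but p = 0.07 at 54, and it falls short across the whole assumed pregnancy range. A true r of 0.30 would be significant with probability about 0.70 (n = 68) or 0.60 (n = 54) in preconception, but only about 0.41 at 34 pregnancies. If the two tests are treated as independent, both succeed with probability of roughly 0.24 to 0.29.
- *Nothing checks whether urine responds to change.* The 2-month objective and the comparison of metabolites over time do look at change, and an arm-level comparison with the C-HEI can be read from planned results. Only the direct comparison of changes in the two scores is absent.
- *Arm mixing could create the correlation.* On its own it gives about 0.13, below every threshold in the table. It also presupposes that the urine score responds to the intervention.

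It is also fair that confidence intervals, per-visit reporting and group adjustment are often left to an analysis plan, which is not shown here. Their absence is not the fault raised. They are part of the repair.

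**Conclusion.** The point holds in limited form. The step from correlation in both periods to sole measure does not follow from the analysis described. Under the significance reading, the qualifying correlation could be as low as 0.24–0.27 in preconception and 0.29–0.44 in pregnancy, which is 6–7% and 9–20% shared variance, with confidence limits reaching zero. The pregnancy figures depend on an assumed 45 to 20 women. Whatever strength is found, agreement in change between the two scores is not examined, and replacing a change-based endpoint requires it. The primary endpoint, the sample size and the trial's main conclusion are untouched. Severity is minor.

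**What to change.** **Secondary Outcome Analysis.** Report r with its 95% CI separately at baseline, 2 months and 24–26 weeks, adjusted for study group after baseline. Add the within-woman correlation between the baseline-to-2-month changes in the two scores, also adjusted for group.

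**Discussion.** Replace the sole-measure inference with a statement that a correlation of levels supports urine as a complement to recall. Say that replacement would also need agreement in change and a strength criterion set in advance by the investigators. The documents give no basis for a particular value. A lower confidence limit of 0.5, for example, would need an observed r of about 0.66 at 68 women and 0.72 at 34, so the choice should be deliberate.

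**Cost.** Under Variables and Data Collection, both measures are already taken in both arms at baseline and 2 months, so this needs only wording and a few lines of analysis. The downside is that the replacement claim becomes harder to make at this sample size. Change scores are also noisier than levels, so a low change correlation should be read with its interval and not taken as proof that urine fails.

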### Trial Design and Setting

This study is a multicenter open label parallel group randomized controlled trial coordinated at the Research Centre of the Centre hospitalier universitaire de Sherbrooke (CR-CHUS) in Sherbrooke, Quebec, Canada. The Province of Quebec has a population of 8.5 million. In 2014 overweight and obesity rates were 27 and 15% for adult women and 41 and 18% for adult men, respectively (49). Participants will be recruited from the Sherbrooke and Quebec City regions. The obstetrical care of women from Sherbrooke and Quebec City is provided by general practitioners, midwives, and obstetricians in outpatient clinics. The CHUS is a regional tertiary care center where ~2,800 deliveries are performed annually. The CHU de Québec Université Laval is a regional tertiary center where ~7,500 deliveries are performed annually at two sites, the Centre Hospitalier de l'Université Laval and the Hôpital Saint-François d'Assise.

An explanatory design has been chosen to rigorously evaluate the potential benefits of the *Healthy for my Baby* intervention (50). Masking of the research team and participants to the intervention will not be possible given the nature of the study. Couples will be randomized to the intervention or control group in a 1:1 ratio. The randomization list was generated independently by the CRCHUS' biostatistics service using a computerized unstratified blocked randomization with blocks of random sizes 2–6. The group allocation sequence was sent directly to the mobile application programming team who input it into the mobile application software. The mobile application website is hosted on the PIERCE server, a secured research platform developed by the local CRED medical informatics working group. Once participants have provided written consent, completed the trial enrollment form, and completed baseline assessment, their mobile application profile will be created by the research assistant which will trigger randomization to a treatment group. Participants will receive the result of their group allocation by email with a link to install the appropriate version of the mobile application.

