### Interventions

#### Intervention Arm

Participants randomized to the intervention group will receive the *Healthy for my Baby* intervention. This intervention is based on the Control Theory, according to which behavior can be regulated by engaging oneself in an active process centered on establishing and following-up specific goals (51). Couples will initiate the preconception intervention by participating in a 60-min motivational interview (MI) session on healthy lifestyle habits (52). At the end of this session, each member of the couple will have set specific SMART lifestyle goals (53) in at least two of five key areas: nutrition, physical activity, sleep, well-being (stress, anxiety), and environment (tobacco use, drug use, alcohol consumption, or other toxic substances). Lifestyle goals will be tailored to each participant based on the priorities verbalized in the motivational interview with the aim of improving compliance with Canadian guidelines for diet, physical activity, sleep, and consumption of alcohol (54, 55). Participants will then have access to a mobile phone application designed by our research team that will help them achieve three goals in different dimensions at a time through daily self-monitoring (Supplementary Figure 1). Self-monitoring has been shown in a meta-regression analysis to be the most effective behavior change strategy to improve diet and physical activity (56). In addition to allowing participants to track their lifestyle goals, the mobile application includes references on healthy habits for preconception and pregnancy, a research visit calendar, a fertility tracker, links to videos on different aspects of parenthood, and a platform to contact the research team.

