#### Control Arm

Participants randomized to the control group will receive standard advice on healthy lifestyle habits as provided by their usual care provider. Usual care in preconception is the same as that of healthy adults and does not specifically involve access to lifestyle interventions. In the Estrie region, which includes the Sherbrooke area, individuals with obesity, or overweight and a cardiometabolic diagnosis, have access to a free-of-charge program at local health centers, which includes group sessions with a limited individual nutritional intervention. However, these services are neither integrated nor targeted at preconception care and are rarely used by these couples. Participation in these sessions, or in any other lifestyle programs or consultations with a lifestyle professional will be documented. In addition to routine obstetrical care, women with GDM are typically followed by a nutritionist, and those who present comorbidities such as hypertension or morbid obesity may be followed by a nutritionist. Participants in this group will have access to a simplified version of the mobile application containing only the research visit calendar, the fertility tracker, videos on parenthood, and the platform to contact the research team. This version of the application does not contain any information on healthy lifestyle habits.

Participants from both study groups will be allowed to participate in the existing local *Taking Care of your Health* educational program if they are eligible or to consult any health care professional if clinically required. However, they will be asked not to voluntarily begin a similarly intense lifestyle program during the trial.

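### The primary diet score is unmasked self-report with one arm coached, and the stated urine analyses do not set the objective diet measure beside it by study group.

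*Protocol article*

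**What the plan says.** **Masking.** Under Trial Design and Setting: "Masking of the research team and participants to the intervention will not be possible given the nature of the study".

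**What each arm receives.** The Intervention Arm section describes motivational interviews in which participants set "specific SMART lifestyle goals (53) in at least two of five key areas: nutrition, physical activity, sleep" and further areas, "with the aim of improving compliance with Canadian guidelines for diet, physical activity, sleep, and consumption of alcohol". Goals are logged daily in an application that the research team can read, and participants who miss goals are contacted. Of the control application, the Control Arm section says: "This version of the application does not contain any information on healthy lifestyle habits".

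**Primary measure.** The Diet Quality section builds the C-HEI 2007, a score of adherence to the 2007 Canadian Food Guide, from three online 24-hour recalls per time point. In preconception these fall at baseline and at 2, 4 and 6 months.

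**Stated mitigation.** The limitations paragraph of the Discussion first concedes that masking is impossible. Its answer has two parts. Diet is to be captured by online recall together with urine. For the remaining self-reported outcomes it states that "the other lifestyle habits scores will be collected with the use of self-reported questionnaires to limit social desirability".

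**Urine.** Samples are taken in preconception at baseline and 2 months only. The Objectives list the intervention's impact on urinary indicators at 2 months as a secondary objective. Secondary Outcome Analysis compares about 40 targeted metabolites between baseline, 2 months and 24–26 weeks of pregnancy, without naming study group. It adds: "The correlation between the metabolite derived diet quality score and the C-HEI score will be evaluated using Pearson's correlation".

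**The concern.** Coaching and scoring point the same way. Women in the intervention arm discuss goals with the team, log them where the team can see them, and know what a good answer looks like. Control women receive none of this from the trial. If coached women report a better diet than they eat, the C-HEI difference grows with no change in diet. Completing a questionnaire alone takes away the interviewer, but not the knowledge of which answers are hoped for.

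The trial does hold a measure that does not depend on what women report. Set beside the C-HEI by arm at 2 months, it would help to show whether a reported gain reflects eating. As written, the targeted urine analysis describes change over time, and the only link between urine and recall is a correlation. The Discussion makes a larger trial depend on positive dietary change, so it matters whether that change was eaten or only reported.

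**Working it through.** **1. Reproduce the plan's figure.** Inputs from Sample Size Calculation: difference 10 points (10% of a 100-point score), SD 13, alpha 5% (taken as two-sided), power 80%, attrition 20%.

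- n per arm = 2 × (1.960 + 0.842)² × 13² / 10² = 26.5, so 27.
- 27 / 0.80 = 33.75, so 34 per arm and 68 in total.

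Both match the article. Power at 27 per arm is 80.7% by the normal approximation and 79.2% by the noncentral t.

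**2. What over-reporting alone would do.** Suppose no true diet effect and a uniform over-report of b points in the intervention arm. The article gives no figure for b, so the values are assumed. The standard error is 13 × √(2/27) = 3.54, the noncentrality is b / 3.54, and there are 52 degrees of freedom.

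| Assumed b (points) | b / 3.54 | Significant at two-sided 5% |
|---|---|---|
| 0 | 0 | 5.0% |
| 2 | 0.57 | 8.6% |
| 3 | 0.85 | 13.2% |
| 4 | 1.13 | 19.9% |
| 5 | 1.41 | 28.4% |
| 10 | 2.83 | 79.2% |

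This uses the simple two-group comparison behind the sample size, not the planned mixed model.

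**3. Can the correlation show it?** Within an arm, adding a constant to every recall score leaves Pearson's r unchanged. Pooled over two equal arms with common SD σ and within-arm correlation ρ, a pure recall shift b gives

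r = ρ / √(1 + b² / 4σ²).

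With ρ = 0.5 (assumed), σ = 13 and b = 10, r = 0.5 / √(1 + 100/676) = 0.47. With b = 5 it is 0.49. Simulation at 27 per arm (20,000 runs) agrees closely:

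| Assumed within-arm ρ | No effect, no bias | True effect 10 | Pure bias 10 |
|---|---|---|---|
| 0.3 | 0.30 | 0.39 | 0.28 |
| 0.5 | 0.50 | 0.56 | 0.46 |
| 0.7 | 0.70 | 0.74 | 0.65 |

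At ρ = 0.5 the 95% simulation ranges overlap widely (0.35–0.72 for a true effect, 0.23–0.66 for pure bias). The pure-bias correlation is still significant in 95% of runs.

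**4. Can a between-arm comparison of urine show it?** In the same simulation, a two-group test of the urine score rejects in about 79% of runs with a true 10-point effect and about 5% with pure bias. This assumes that the urine score has the same SD and responsiveness as the C-HEI. If it registers only half the shift, the table in step 2 gives about 28%, so a null urine result would then be weak evidence of over-reporting.

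**The case against.** Most of the opposing case narrows the point, and these parts stand.

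- **Scope of the sentence.** A reader might infer that the article claims self-report protects the C-HEI. It does not: the clause concerns the other lifestyle scores, and for diet the same sentence cites urine as well as recall. Self-completed tools do remove one route of social desirability, the unmasked interviewer.
- **An objective check is intended.** A reader might infer that the plan has no means of separating better eating from better reporting. The 2-month urinary objective is about the intervention's impact, and the general provision for t-tests or Mann-Whitney tests on other secondary outcomes might cover the metabolite score. The gap is that the analysis written for urine names time points and not study group.
- **Purpose of the correlation.** A reader might take it as a check on over-reporting, or as validating both measures. The Discussion uses it only to support the biomarker for future studies: "If the metabolite derived diet quality score can be correlated with the C-HEI both in preconception and pregnancy". That it pools the arms is also an inference, since the text names no group. A correlation within each arm would be equally blind to a constant shift.
- **Strength of the mechanism.** Nutrition is one of five goal areas, so not every coached woman need set a diet goal. Women also collect their own urine, which reflects roughly the preceding 72 hours, so eating could change around sampling.

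What does not answer the point is that any unmasked self-report trial shares this risk. Here an objective measure is already collected, and the stated analyses do not use it by arm.

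**Conclusion.** The concern holds in a limited form. The C-HEI is unmasked self-report, with coaching in one arm towards the guidance it scores, and self-completion does not remove reporting bias that differs by arm. The targeted urine analysis as written does not deliver the between-arm objective set for 2 months, and a correlation cannot fill that gap.

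The documents do not show that over-reporting will occur, or how large it would be. The 13% to 28% range rests on assumed shifts of 3 to 5 points, no true effect, 27 per arm, SD 13 and a simple two-group test. Nor do they support saying that the trial cannot detect the problem at all: the 2-month urine data could help, within their noise. No preconception urine is taken after 2 months, so nothing objective on diet stands beside the C-HEI at 4 and 6 months.

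**What to change.** 1. **Discussion, limitations.** Say that the C-HEI and the other self-reported scores are unmasked and may be over-reported in the coached arm. Self-completion can be credited with reducing interviewer pressure, and no more.
2. **Secondary Outcome Analysis.** State that the baseline-to-2-month change in the metabolite-derived diet score is compared between arms, adjusted for baseline, with an estimate and 95% confidence interval. Report it beside the between-arm change in C-HEI at 2 months, both in baseline-SD units.
3. **Interpretation.** Present this as supportive evidence. If the C-HEI favours the intervention and the urine score does not corroborate it, describe the result as a change in reported diet quality. Note that the urine score is noisy and exploratory and stops at 2 months in preconception.

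Two tempting alternatives should be avoided. Correlations by arm cannot show a constant shift. A rule that asks only whether the urine score moves in the same direction would miss about half of pure-bias results, because with no true effect the sign is favourable about half the time.

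The cost is a reworded sentence and one extra comparison on data already planned, with no added visits, samples or participants. The downside is that a positive claim may need more cautious wording.
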